## **SUMMARY**

Worldwide, over 2 billion people suffer from worm infections (hookworm, *Ascaris* and *Trichuris*, collectively referred to as soil-transmitted helminths (STHs)) in developing countries. STHs contribute to the overwhelming burden of poverty and deprivation in areas where adverse health, social, economic, education and other related factors predominate. STH infection in childhood results in short-term and lifelong disability, including malnutrition (e.g. underweight, stunting and wasting), cognitive impairment and increased susceptibility to other infection, among others. Mass deworming programs in school-age children are recommended by the World Health Organization (WHO). WHO also recommends deworming of preschool children (as of 12 months of age) in endemic areas; however, the benefits of deworming on improving growth and development, especially in the 12-24 month age group, have been inadequately studied. This knowledge is crucial because, with appropriate nutrition and health interventions, all children have a similar potential for healthy growth and development, provided that such interventions occur in the critical window of opportunity before the age of two.

Therefore, this double-blind randomized controlled trial will assess the benefit of deworming (mebendazole), integrated into routine child health care visits in a highly STH-endemic area (Iquitos, Peru), on the primary outcome of weight gain. Timing, frequency and impact of deworming will be considered. A total of 1760 children will be recruited at their routine 12-month check-up visit and randomly assigned to one of four intervention groups: Group 1 will receive usual care and mebendazole (single dose 500 mg) at their 12-month visit and usual care and a placebo tablet at their 18-month visit; Group 2 will receive usual care and a placebo tablet at their 12-month visit and usual care and mebendazole at their 18-month visit; Group 3 will receive usual care and mebendazole at both their 12-month and 18-month visit; and Group 4 will receive usual care at both their 12-month and 18-month visit. Usual care will consist of age-appropriate immunizations, supplements and other Peruvian Ministry of Health-recommended interventions. All children will be followed up to their 24-month visit and all will be given mebendazole at that time.

Additional secondary outcomes include length gain, motor and cognitive development and STH prevalence and intensity.

Improving child health is a priority area in global health research and a focus of the Millennium Development Goals. Early preschool-age children are at the most critical stage of growth and development and have been neglected in deworming programs. It is anticipated that the results will inform evidence-based policy on the provision of an integrated health package for young children in endemic areas and ultimately contribute to the reduction of health inequities in this vulnerable group.

## **CONTEXT OF THE PRESENT PROTOCOL SUBMISSION**

The present proposal builds on past research conducted by all co-applicants in the fields of epidemiology, population health, intervention research, biostatistics, infection and nutrition, and especially, research conducted in Peru. This research has been interdisciplinary in nature, some of it participatory, some of it qualitative, and most, quantitative. The focus has been on malnutrition (eg. stunting, anemia) and the neglected tropical diseases of poverty, in particular, soil-transmitted helminth infections.

The current research question arises from both a global and a local evidence base on deworming. In 1996 and 1997, respectively, [name] and [name] conducted parasite surveys to inform the national deworming program in Guinée, West Africa . This research contributed to national health policy, such that deworming activities at the district level were scaled up to national level within two years. With two other colleagues, in 2002, [name] and [name] co-authored a WHO manual on Helminth Control in School-Age Children which is a resource guide for managers of control programs . (A second edition of this book is currently being prepared.) Both have been active in continuing deworming intervention research. Global initiatives, including that of WHO, now recognize the critical impact of deworming in pre-school children, in terms of its impact on growth and development.

Peru-based research began in 2001 with [name], [name] and [name] addressing the problem of anemia during pregnancy, half of which is generally attributable to worm infections. A double-blind randomized controlled trial, enrolling over 1000 pregnant women, was conducted to investigate the value of deworming and iron supplementation in reducing maternal anemia and improving infant birthweight . The database from this research has provided the opportunity to address other research questions eg. . Subsequent (published) research has included a survey of over 1000 schoolchildren living in Belén, a community of extreme poverty close to Iquitos, where we found that over one-third of Grade 5 students were stunted ; and by a household survey which documented underweight and wasting in ~ 30% of preschool children . In the analysis of the pre-school-age child data, we also demonstrated the differences between the new WHO growth standards for pre-school children and the 'old' NCHS-CDC standards. Current research activities involving [name], [name], [name], and [name] are partnered with the local Ministry of Health. They focus on evaluating the effectiveness of a set of health system-based nutrition educational interventions aimed at pregnant women and new mothers (to reduce infant and child malnutrition). Several manuscripts are already in preparation from this research . In addition, our research now specifically includes gender analyses  and health equity considerations eg. .

### **LOCATION OF STUDY CONDUCT**

The study will be conducted in neighbouring districts around the city of Iquitos, the capital of the Loreto region in the Peruvian Amazon. Highly STH-endemic areas in which the study will be conducted have been identified, including Belén, Punchana and San Juan. The principal investigator and several co-investigators have a long-standing research collaboration in these areas. The results of the study will be relevant to other STH-endemic areas throughout the world.

### **STUDY RATIONALE**

Improving child health is a priority area in global health research and a focus of the Millennium Development Goals (MDGs). Early preschool-age children (i.e. less than two years of age) are at the most critical stage of growth and development and have been neglected in deworming intervention programs. The proposed study will determine the effectiveness of the timing and frequency of deworming on health and nutrition outcomes in children 12 to 24 months old, evidence which is currently lacking. The results will inform evidence-based policy on the incorporation of deworming activities into existing integrated health packages for young children, which currently include growth and development monitoring, vaccinations and

micronutrient supplementation. The trial will be conducted in a community of extreme poverty in a tropical area of Peru with results of relevance to other parts of the country, most of the LAC region, and STH-endemic areas of Africa and Asia. Scaling-up of interventions is needed in this age group to improve child nutrition on a global scale, to help achieve the MDGs, and ultimately to contribute to the reduction of health inequities in this vulnerable group. These types of integrated, inter-sectoral prevention and control measures using existing health infrastructure are widely recognized as being essential to improve health and nutrition, reduce NTD burden and make progress towards the MDGs.

## **BACKGROUND**

### **Malnutrition in early preschool-age children**

Malnutrition is the leading cause of mortality in preschool-age children in low and middle income countries (LMICs), with over 150 million children suffering from one or more forms of malnutrition, including stunting, underweight and /or wasting. Malnutrition also predisposes to infection, creating a vicious infection-malnutrition cycle that contributes to over 35% of the disease burden of early childhood. Infection, including worm infections, and poor quality and low availability of food, resulting in micronutrient and other deficiencies, are the primary causes of malnutrition in childhood. Early childhood is a critical time for growth faltering (related to weaning), and, as mobility increases, for early acquisition of infectious pathogens (through food, water and the environment). A recent study in 54 countries confirmed that interventions to prevent child malnutrition *must occur during the first two years of life* to prevent further growth deficits. Interventions at this stage are essential to prevent both short- and longer-term adverse effects. Stunting, in particular, is thought to be irreversible after 36 months of age. Improving the health of the youngest children is integral to achieving the Millennium Development Goals (MDGs). Evidence from the World Health Organization (WHO) Child Growth Standards demonstrates that, with appropriate nutrition and health interventions, all children have a similar potential for healthy growth and development; however, children living in areas of greatest poverty suffer the most from health and social inequities due to increased disease burden and lack of access to necessary health interventions and services.

### **Soil-transmitted helminths and malnutrition in early preschool-age children**

Interventions that can help reduce child malnutrition within the first year of life include exclusive breastfeeding, micronutrient supplementation and vaccinations. After one year of age, growth faltering often increases and children in developing countries continue to deviate even further from normal growth standards. At this stage, it is critical to keep infection to a minimum and appropriate interventions should be incorporated into routine child health care packages. In developing countries, the soil-transmitted helminths (STHs), or worm infections, are a significant contributor to poor health and malnutrition in all age groups. The STHs are a cluster of three diseases, *Ascariasis* (roundworm infection), *Trichuriasis* (whipworm infection) and hookworm infection. STHs are one of the most important Neglected Tropical Diseases (NTDs) and are the most common infections with over 2 billion people infected worldwide. An estimated 5-10% are children in the most critical growth period under two years of age. The burden of disease attributable to STH infections can be even more pronounced when children are exposed to these infections at an early age. As the STHs are spread through contaminated soil, food and hands, children begin to acquire these infections as they become mobile and begin to explore the environment. *Ascaris* and *Trichuris* are the predominant STH

infections in early childhood.

The main adverse effect of STH infection in childhood is malnutrition. Other health consequences include cognitive impairment and increased susceptibility to infections, among others. STH infection leads to malnutrition through nutrient malabsorption, blood loss and loss of appetite. WHO recommends large-scale deworming interventions, using a single-dose anthelmintic (i.e. deworming) treatment, for the high-risk groups of school-age children, pregnant women and preschool-age children in endemic areas. These interventions are often incorporated into schools (for school-age children) or prenatal care programs (for pregnant women). Children under two years of age had traditionally been excluded from deworming interventions as the burden of STH infection was perceived to be low in this age group. There has been increasing empirical evidence however, which shows that STH prevalence can be high in early childhood. In a study in the Democratic Republic of the Congo, both *Ascaris* and *Trichuris* were prevalent in over 50% of children under two years of age. In Belén, a community of extreme poverty in the Peruvian Amazon, the prevalence of *Ascaris* or *Trichuris* was only 4% in infants at 6 to 9 months of age, but rose to 30% at 12 to 14 months of age. In this same area, the STH prevalence increased to 50% by 18 months of age ([name], unpublished data). It is becoming increasingly recognized that STH infection in early childhood may have important adverse effects as the parasites take up a greater proportion of the body in younger children. WHO recommends including children 12 to 24 months of age in deworming activities in endemic areas, using either mebendazole (usual single-dose of 500 mg) or albendazole (reduced single-dose of 200 mg). (While some studies have included infants below 12 months of age in their study populations, WHO recommends that the minimum age for deworming interventions be 12 months.) Despite these recommendations, the benefit of deworming in this age group has been inadequately studied and coverage is still suboptimal. The global proportion of at-risk preschool-age children currently being dewormed is estimated to be on the order of 21%, with a low of 11% coverage in the Latin America and Caribbean (LAC) region.

### **Evidence on deworming in 12 to 24 month old children**

A Cochrane review was published in 2008 looking at the effects of targeted deworming (i.e. targeted to high-risk groups of school-age and preschool-age children) on growth and school performance. A total of 34 RCTs were included in the review; none focusing exclusively on the 12 to 24 month age group. Of the 34 trials, only two studies: 1) included children between 12 and 24 months of age in their child study populations; 2) were conducted in healthy children; 3) examined anthropometric outcomes (e.g. weight and/or height/length); and 4) compared either albendazole or mebendazole (the two drugs recommended by WHO for STH infection in children under two years of age) to placebo or usual care. Unfortunately, the child study populations in these two studies included children up to 7 years and 8 years of age, respectively, and reported results were not age-disaggregated; therefore, the effect of deworming in the 12-24 month age group is unknown. A recent meta-analysis was published by Hall et al, also in 2008, examining the effects of STH infection and deworming on growth and/or nutrition of children up to 18 years of age. This meta-analysis included 19 trials, the number being restricted to those conducted in areas where the prevalence of STH was over 50%. No trial reported specific data on 12-24 month-old children. One additional study, not included in either the Cochrane or the Hall reviews, found a significant benefit of albendazole on weight gain in children 1 to 5 years old, but, again, it was not possible to attribute this benefit to any particular age group.

Although these previous studies and reviews provide some evidence on the benefits of deworming on nutrition and health in children *over* two years of age, there are substantial limitations to extrapolating their results to children *under* two years of age. Of the previous studies, none have examined the effect exclusively in children 12 to 24 months or provided pertinent age-disaggregated data. With wide age ranges of children included in the sample size (up to 8 years of age), previous studies would have been underpowered to detect statistically significant effects of deworming in any particular age subgroup. No studies have determined the most appropriate time for deworming in children less than two years of age. Considering that STH prevalence is generally lower at 12 months of age ([name] et al, manuscript under review), but can increase rapidly by 18 months of age ([name], unpublished data), this information is necessary to determine the time at which deworming can have maximum health and nutrition benefits. An additional limitation is that most studies used albendazole for the dewormed group; however, in the younger age groups who have more *Ascaris* and *Trichuris* infection, and negligible hookworm infection, deworming with mebendazole, rather than albendazole, would be more efficacious and produce a greater impact . Lastly, as these younger children are undergoing rapid growth and development, appropriate indicators need to be measured to demonstrate the additional benefit that deworming may have, over and above the normal growth which takes place at this stage.

The Cochrane review, the meta-analysis and other publications have highlighted the limitations of previous studies (e.g. inadequate allocation concealment and blinding, high loss-to-follow-up, clustering of observations, inadequate data analyses, etc.) and recommended that better-designed RCTs are necessary to provide appropriate evidence on the benefits of deworming on multiple health and health-related outcomes . In particular, evidence on the benefits for preschool-age children was deemed to be necessary for future intervention planning . Considering the unique nutritional demands and growth patterns of younger children, aggregated results from older children do not provide an appropriate indication of the potential benefit of deworming on growth and nutrition in younger age groups who are in a critical growth window. Based on the limitations of previous studies, it is clear that methodologically sound research is needed to provide evidence on the benefit of incorporating deworming into routine health services for children between the ages of 12 and 24 months.

## **OBJECTIVES**

The principal objective is to determine the effectiveness of a deworming intervention, in terms of timing, frequency and impact, to improve weight gain in infants between 12 and 24 months of age.

The secondary objectives are to determine the effectiveness of a deworming intervention, in terms of timing, frequency and impact, to improve length gain, cognitive and motor development and to reduce prevalence and intensity of STH infection in infants between 12 and 24 months of age.

## **METHODS**

### **Research Design**

The timing, frequency and impact of a deworming intervention, incorporated into health services during routine Growth and Development ('Crecimiento y Desarrollo' or CREDE) visits, will be evaluated in children 12 to 24 months old living in a highly STH-endemic area of the Peruvian

Amazon using a double-blind randomized controlled trial design. There will be four intervention groups randomized to different deworming schedules: 1) usual care and deworming treatment at the 12-month visit and usual care and placebo at the 18-month visit, 2) usual care and placebo at the 12-month visit and usual care and deworming at the 18-month visit; 3) usual care and deworming at the 12-month visit and usual care and deworming at the 18-month visit; and 4) usual care and placebo at both the 12 and 18-month visits. All children will receive deworming at 24 months of age. Weight, length, cognitive and motor development and STH infection will be evaluated at 12, 18 and 24 months of age.

### **Study community**

The study will be conducted in neighbouring districts around the city of Iquitos, the capital of the Loreto region in the Peruvian Amazon. Three districts of extreme poverty have been identified (Belén, Punchana and San Juan) where worm infections are highly endemic and malnutrition prevalence is high. The prevalence of underweight in children 12 to 14 months of age was recently estimated to be 31% and STH prevalence to be 29% ([name] et al, manuscript under review). The STH prevalence doubles by 18 months of age ([name], unpublished data) and reaches over 85% in school-age children. Previous research in the area has shown a significant association between STH infection and poor growth in both preschool- and school-age children ([name] et al, manuscript under review). Both STH infections and malnutrition have been identified as priority concerns by stakeholders in the community. At present, there is no routine deworming for preschool-age children.

Preschool-age children attend routine government-sponsored CREDE visits at health clinics in Peru once-monthly from birth to 12 months of age, and every two months from 12 to 24 months of age (with less frequent visits continuing through preschool-age). Each health centre has one to two nurses who are responsible for CREDE check-ups. During routine CREDE visits, anthropometric measurements (e.g. weight and length) are taken, developmental milestones are recorded (e.g. gross motor skills), and children receive routine age-appropriate immunizations and supplements. Parents also receive nutrition and other health counselling for their child.

### **Study population**

The study population will include children attending their routine 12-month CREDE visit (at which time measles vaccination is scheduled) in the study area. Using data provided by the Peruvian Ministry of Health, eight study health centres (“Centros de Salud”) have been identified in high-risk (i.e. high STH prevalence) areas neighbouring Iquitos. These include Centros de Salud: 1) 06 de Octubre, 2) 09 de Octubre, 3) Belén, 4) Cardozo, 5) Bellavista de Nanay, 6) Masusa; 7) 01 de Enero and 8) Fernando Lores.

The inclusion and exclusion criteria for participating children are as follows:

**Inclusion criteria:** 1) children attending any one of the eight study health centres for their 12-month CREDE visit (for feasibility and to ensure recruitment of children from highly STH endemic areas); 2) children living in or near the Belén, Punchana or San Juan district (to ensure recruitment of children from highly STH endemic areas, as well as to ensure high follow-up)

**Exclusion criteria:** 1) children who are attending the clinic for suspected STH infection (as they may require immediate, specific treatment); 2) children who have received deworming treatment

in the six months prior to randomization (as the effect of previous treatment may interfere with the effect of the randomized treatment); 3) parents planning to move outside of the study area within the next 12 months (to maximize participation rates and follow-up); 4) children under 12 months of age (as treatment is not recommended for this age group), or 14 months of age or older (to ensure participants are at a comparable growth and developmental stage); and 5) children with serious congenital or chronic medical conditions and who would be considered by the attending staff not to benefit from deworming.

### **Sample size**

Sample size calculations are based on the smallest meaningful difference in mean weight gain between intervention groups. From pilot data, we anticipate that the mean weight gain  $\pm$  standard deviation between 12 and 24 months in the group receiving usual care and placebo at both time points will be approximately 2.0 kg  $\pm$  0.8 kg. Based on previous research, we expect an improvement of 0.5 kg in weight gain in the group receiving deworming at 18 months of age (with 50% STH prevalence) compared to the group receiving usual care and placebo at both 12 and 18-month visits (i.e. 2.5 kg) and 0.7 kg improvement in weight gain in the group receiving deworming at both 12 and 18 months of age (i.e. 2.7 kg) [51]. This difference takes into account effect dilution based on treating groups of both infected children (who will benefit directly from the deworming treatment) and non-infected children (who may not benefit directly from the deworming treatment). The mean weight gain in those receiving usual care and deworming at the 12-month visit is estimated to be half of the gain in the group receiving usual care and deworming at 18 months of age (i.e. 2.25 kg).

In order to have 80% power to detect a difference in mean weight gain of 0.2 kg (the smallest meaningful difference we are aiming to detect), assuming a common standard deviation of 0.8, and using a one-way ANOVA which accounts for pairwise multiple comparisons using the Tukey correction, the estimated sample size per group is 366 children. Taking into account a 20% attrition rate after 12 months of follow-up, the required sample size is estimated to be 1760 children, or 440 children per group (MCG4 Software, Ohio University, 2008).

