### **Loss to follow-up**

A 20% rate of attrition has been estimated after 12 months of follow-up. This estimate is based on over eight years of experience in the area which has included follow-up with pregnant women (less than 10 % loss to follow-up over 7 months)  and new mothers (less than 18 % loss to follow-up after 8 months). High participation rates and follow-up will be encouraged by providing reimbursement to cover travel costs (the equivalent of a roundtrip bus ticket) for each of the two follow-up visits (an incentive previously acceptable to both Canadian and Peruvian ethics committees). Mothers have a booklet that they bring to each routine CREDE visit so that essential information can be recorded and the following visit can be scheduled. This should also facilitate the scheduling of the follow-up visits. A higher attrition rate of 20% has been accounted for in the proposed study due to the longer follow-up time of 12 months.

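### The 20% attrition allowance multiplies 366 by 1.2 instead of dividing by 0.8, so 440 per group leaves 352 evaluable and about 77% to 78% power for 0.2 kg, a modest shortfall from 80%

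*Protocol*

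**What the plan says.** The Sample size section of the protocol fixes the design target with the words "In order to have 80% power to detect a difference in mean weight gain of 0.2 kg". It adds "assuming a common standard deviation of 0.8" (kg) and specifies "using a one-way ANOVA which accounts for pairwise multiple comparisons using the Tukey correction". From these inputs it reports that "the estimated sample size per group is 366 children". After an allowance for 20% attrition over the 12 months of follow-up, it concludes that "the required sample size is estimated to be 1760 children, or 440 children per group".

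The Loss to follow-up section gives the same rate: "A 20% rate of attrition has been estimated after 12 months of follow-up". It supports the rate with loss percentages from earlier work in the area (under 10% over 7 months, under 18% after 8 months) and explains that 20% was chosen because follow-up here is longer. The Summary repeats the total: "A total of 1760 children will be recruited".

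The same Sample size section expects mean 12-month weight gains of 2.0 kg (placebo at both visits), 2.25 kg (deworming at 12 months), 2.5 kg (deworming at 18 months) and 2.7 kg (deworming at both).

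**The concern.** Attrition is a share of the children enrolled. To finish with 366 after losing 20%, the enrolled number times 0.8 must equal 366. Adding 20% to 366 and then losing 20% of the larger number does not return to 366. The stated 440 matches the first operation and not the one required.

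At stake is whether the enrolment target delivers the power claimed for it at the protocol's own planning rate. The 0.2 kg target equals the expected gap between deworming at both visits and deworming at 18 months only. That contrast bears on frequency of deworming, which the principal objective names.

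**Working it through.** **Inputs from the protocol (Sample size; attrition also in Loss to follow-up).** Difference 0.2 kg; SD 0.8 kg; four groups, hence six pairs; Tukey correction; target power 80%; 366 evaluable per group; attrition 20%; 440 per group, 1760 in total.

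**Input assumed.** Alpha and sidedness are not stated in the protocol. A two-sided familywise 0.05 is used for the power figures. Steps 2 and 3 do not need it.

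**1. Reproduce 366.** Power for one pair under the Tukey procedure comes from a noncentral t distribution with 4(n − 1) degrees of freedom.
- Critical value: q(0.95; 4, 4(n − 1))/√2 = 2.572 for n in this range.
- Noncentrality: 0.2 / (0.8 × √(2/n)).
- At n = 366 the noncentrality is 3.382 and power is 79.1%.
- Power reaches 80% at n = 373.

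So 366 is reproduced to within 2% in size and 1 point in power. Other methods fit less well: unadjusted 252, Bonferroni over three pairs 336, omnibus F (two groups 0.2 kg apart, the others midway) 350, Šidák over six pairs 386, Bonferroni over six pairs 388.

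**2. Reproduce 440.**
- 366 × 1.2 = 439.2, rounded up to 440; 440 × 4 = 1760, the stated total.
- Required operation: 366 / 0.8 = 457.5, so 458 per group; 458 × 4 = 1832, which is 72 more.

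**3. What 440 delivers.**
- 440 × 0.8 = 352 evaluable per group; 366 − 352 = 14 short.
- 440 covers 366 only if attrition is at most 1 − 366/440 = 16.8%.

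**4. Power for 0.2 kg at 352, on two bases.**

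| Basis | Power at 366 | Power at 352 | Cost of the attrition step |
|---|---|---|---|
| Direct calculation (noncentrality 3.317, critical value 2.572) | 79.1% | 77.2% | 1.9 points |
| Critical value set so that 366 gives exactly 80% (2.540, normal approximation) | 80.0% | 78.1% | 1.9 points |

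**5. Difference detectable with 80% power at 352.**
- Direct: (2.572 + 0.842) × 0.8 × √(2/352) = 0.206 kg.
- Taking 366 as exact: 0.2 × √(366/352) = 0.204 kg.

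**6. The six expected contrasts.** Means of 2.0, 2.25, 2.5 and 2.7 kg give pairwise differences of 0.20, 0.25, 0.25, 0.45, 0.50 and 0.70 kg. At 352 per group, power is 94.2% for 0.25 kg and above 99.9% for 0.45 kg or more. Only 2.7 versus 2.5 kg sits at the 0.2 kg target.

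**7. Enrolment on each basis.**
- 458 per group restores 366 evaluable, which gives 79.1% by direct calculation.
- 80% by direct calculation needs 373 / 0.8 = 466.25, so 467 per group; 467 × 4 = 1868.

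**The case against.** The strongest reply is that the effect is small beside the uncertainty of the inputs. The pilot mean and SD are given as approximate. With an SD of 0.78 kg instead of 0.80 kg, power at 352 would be 79.6%. Five of the six expected contrasts, including all three against placebo, keep at least 94%. The outcome, the analysis and control of type I error are untouched. All of this stands, and it sets the severity. It does not make 440 the right result of the protocol's own inputs.

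Could 1.2 have been intended? The Loss to follow-up section treats 20% as the share lost after follow-up, alongside loss percentages from earlier studies. The total is presented as required, and nothing says it was limited by feasibility.

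The omnibus F test alone would keep about 80.3% power at 352. However, the protocol ties its 80% to Tukey pairwise comparisons, and the omnibus calculation gives 350, not 366.

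A reader might infer two stronger things that the protocol does not support:
- That the attrition step alone takes power from 80% to 77%. This sets the protocol's software result for 366 against a separate calculation for 352. On one basis throughout, the step costs about 2 points. The other 0.9 point is the difference between the two methods at 366.
- That 458 per group secures 80%. It secures the protocol's 366 evaluable, and it amounts to 80% only if 366 does.

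**Conclusion.** The point holds as an error in a stated figure, of modest size. The head counts (352 evaluable, 14 short per group, 458 per group needed for 366) follow from the protocol's numbers alone. The power figures, 77.2% to 78.1% for 0.2 kg, rest on an assumed two-sided familywise alpha of 0.05 and on the protocol's SD of 0.8 kg. The shortfall matters for one expected contrast, deworming at both visits versus at 18 months only. It does not show that the trial is underpowered for its comparisons with placebo. This is a correction that should be made, and it does not undermine the design.

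**What to change.** Restate the second paragraph of the Sample size section to say that:
- 440 per group with 20% attrition leaves 352 evaluable per group;
- 352 gives about 77% to 78% power for 0.2 kg with the Tukey correction, or 80% power for about 0.204 to 0.206 kg;
- 366 evaluable requires attrition of at most 16.8%;
- the calculation used a given alpha and sidedness, named in the text.

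If 458 per group (1832) is mentioned, describe it only as the enrolment that restores 366 evaluable; 80% by direct calculation would need 467 per group (1868).

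The cost is one corrected paragraph and a slightly lower stated power, with no extra children and no change to the Summary. If the sponsor chose to raise the target to 458 instead, the cost would be 72 more children and a matching change to the total in the Summary.
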